### Aims of the study

#### Primary aims

Among patients who are regularly followed by a PCP for weight-related diseases targeted for lifestyle management (HTN, DM2 or IGT) and with a BMI ≥ 25 (*targeted diseases group*), we aim at improving, after 18 months of participation in our program (vs. control):the proportion of subjects who have an initial weight management intervention planned;the proportion of subjects who lose at least 5% of their initial weight;weight, waist circumference, lean body mass, blood pressure, physical fitness level, physical activity level and healthy eating habits;biochemical markers of metabolic control and cardiac risk (HbA1c, ApoA and ApoB).
Among patients who are regularly followed-up by a PCP for other health conditions (*regular follow-up group*), we aim at improving after 18 months of participation in our program (vs. control):the proportion of patients who have measured weight, BMI and waist circumference;the proportion of overweight or obese subjects who have an initial intervention planned;weight, waist circumference, lean body mass, blood pressure, physical fitness level, physical activity level, healthy eating habits and markers of metabolic control in overweight or obese subjects.

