**Summary of design of the proposed research project.**

#### Study participants

The Integrated University Health Network, known as the RUIS (*Réseaux universitaires intégrés de santé*), of *Université de Sherbrooke* caters to a population of over 1 million people, encompassing a vast territory including Sherbrooke and Montérégie areas. A pool of at least 35 FMGs in this coverage area did not participate in our Phase-1 project. We will enroll a total of 10 of these FMGs in Phase-2, from which 4-10 members (including at least 2 PCPs and 1 nurse) will participate in our study. When we will initially contact FMGs, we will propose to them a study assessing lifestyle management in primary care and its evolution over time. When we will be in contact with 2 interested FMGs, we will randomize them to the intervention or control groups. The first FMG will then be offered to participate in our obesity management system with preceptorships and virtual learning community. The control FMG will be offered practice monitoring without being aware of the intervention. Participants of each group will sign different consent forms.

As much as possible, we plan to evaluate participants from FMGs pairs of intervention and control groups concomitantly in order to avoid bias related to time of evaluation (due to seasonal effects on weight, campaigns of health promotion, high-impact scientific publications, etc.). Within each FMG, adult patients who present for follow-up will be offered by FMG clerical personnel to have their chart accessed by our team and to be contacted if eligible for the project. If they consent, their chart will be screened to verify if they had, during the past 2 years, at least 4 documented visits for the targeted disease group and at least 2 visits for the regular follow-up group, and if continued follow-up is planned or highly probable in the next 18 months. We aim to include in our study 22 patients per FMG in the targeted disease group, and 24 patients per FMG in the regular follow-up group (total of 460 patients). Patient numbers will be prospectively accrued within each patient category during the recruitment period and before preceptorship delivery for the intervention group, until targeted numbers are achieved. In order to minimize important potential biases, patients will be kept blinded regarding their FMG group and the study objectives related to the evaluation of this intervention.

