#### Intervention

The educative intervention is based on the format developed during our Phase-1 project, i.e. a two-day preceptorship combining theoretical and practical CME, and includes both plenary and nurse- or PCP-specific sessions. At the beginning of our Phase 2 project, we thoroughly reviewed the content of the preceptorship according to expert opinions relevant literature and comments/suggestions from Phase-1 participants. All important topics concerning CCPGO recommendations are covered, such as initial evaluation of patients (including readiness for change), nutritional approach, physical activity, behaviour modification and support to patients, pharmacotherapy, indications for bariatric surgery, obesity in children and adolescents etc. Training is divided into two days that are provided approximately 1 month apart in order for participants to put new knowledge into practice and better identify areas to emphasize during the 2^nd^ day. More than half of the time is devoted to the observation of real patient encounters and case discussions. Sessions are given by members of our research team who are also involved in the Centre Hospitalier Universitaire de Sherbrooke (CHUS) obesity clinic: endocrinologists, pediatric endocrinologist, dietician, kinesiologist and psychologist, according to their field of expertise. The general objective of the preceptorship is to increase self-efficacy and optimize interventions of health professionals regarding obese and overweight patients in complementarity with specialized interdisciplinary resources of the CHUS obesity clinic.

The intervention group also has access to the virtual community previously described, including the web site posting information for health professional and patient tools, monthly virtual meetings where advances in obesity management and difficult cases are discussed, and a discussion forum for participants and obesity experts.

Following expressed needs of participants at the end of Phase-1, we are also providing on-site coaching sessions for FMG participants every three months. They consist of 1 hour discussions with the dietician or kinesiologist of our team who visits the FMG to solve problems with web-site use, solve difficult cases, discuss use of program tools and explore practice changes. The objective is to help participants integrate the virtual community in their practice and answer their clinical questions.

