### Variables and research tools

#### Evaluation of patients

All evaluations will take place at baseline and after 18 months in order to allow sufficient time following the intervention to monitor changes in practice. Although very long term weight maintenance cannot be assessed during that period, we could eventually continue following patients on a longer term as part of future projects.

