#### Medical history and lifestyle interventions

At the end of the study for each study site, thorough medical chart review will be performed using a standardized evaluation grid, also verifying medical and surgical history and medications for the 18 months before and after baseline evaluation of patients. Evaluations and interventions that are proposed to patients will be compared to that proposed in the CCPGO algorithm, and evolution of patients’ weight during the observation period will be recorded.

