#### Evaluation of health professionals (PCPs and nurses)

All evaluations will take place at baseline, T1 (1 month after the preceptorship for the intervention group and 1 month after baseline for the control group) and 12 months after T1 in order to compare the data collected during our Phase 1 study and to compare intervention and control groups. The same questionnaires that we developed and validated will be used to evaluate Aim 3 of this proposal. We have slightly modified some tools based on the results of our Phase 1 project. Results will be correlated to patients’ outcome.

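### Patients get less than the promised 18 months of programme exposure, and the professionals' T1 is counted from a different starting point in each arm

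*Protocol article*

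**What the plan says.** All references are to the protocol article.

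**Patients**
- Primary aims: outcomes in both patient groups are described as measured "after 18 months of participation in our program (vs. control".
- Study participants: enrolment takes place "during the recruitment period and before preceptorship delivery for the intervention group, until targeted numbers are achieved". The target is 22 + 24 = 46 patients per FMG.
- Evaluation of patients: "All evaluations will take place at baseline and after 18 months in order to allow sufficient time following the intervention".
- Intervention: "Training is divided into two days that are provided approximately 1 month apart".
- Medical history and lifestyle interventions: the chart review covers history and medications "for the 18 months before and after baseline evaluation of patients". No other chart window is given.

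**Health professionals**
- Evaluation of health professionals: assessments are at baseline, at "T1 (1 month after the preceptorship for the intervention group and 1 month after baseline for the control group", and "12 months after T1". The stated purposes are comparison with Phase 1 and comparison of the two arms.
- Study participants: members of an FMG pair are to be evaluated at the same time as far as possible, to limit bias from season, health campaigns and publications. The control FMG's T1 is not tied to its partner's training date.

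**The concern.** There are two separate timing problems.

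First, the primary aims describe 18 months of programme participation. The patient's clock starts at a baseline that comes before training at that FMG. Those two statements cannot both hold for a patient enrolled before training. The reason given for choosing 18 months is time after the intervention, yet the interval runs from baseline. At stake is what the primary result means: the effect 18 months after a patient's baseline is not the effect of 18 months of the programme, and unexposed time pulls it towards no difference.

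Second, the professionals' T1 has a different starting point in each arm, and the last evaluation inherits the difference. The knowledge, attitude and vignette tools are repeated at these points. Unequal retest intervals and calendar times then become a difference between arms that is not the intervention.

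**Working it through.** **1. Patient exposure.** Let g be the months from a patient's baseline to training day 1. The article does not state or bound g, so the values below are assumptions. Day 2 falls at about g + 1.

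- Exposure at the final visit, from day 1: 18 − g.
- Exposure at the final visit, from day 2: 18 − (g + 1) = 17 − g.

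| Assumed g | From day 1 | From day 2 |
|---|---|---|
| 0 | 18 | 17 |
| 1 | 17 | 16 |
| 3 | 15 | 14 |
| 6 | 12 | 11 |

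The gap differs between patients and is longest for those enrolled first. Baseline to final visit is 18 months in both arms whatever g is.

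**2. Professionals.** Here g is the months from the professionals' baseline to training day 1. It is also unstated and need not equal the patients' gap.

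- Control: T1 at 1 month; final at 1 + 12 = 13 months.
- Intervention, counting from day 2: T1 at g + 1 + 1 = g + 2; final at g + 14.
- Intervention, counting from day 1: T1 at g + 1; final at g + 13.

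The difference between arms is g + 1 months on the day-2 reading and g months on the day-1 reading, at both T1 and the final evaluation. The two training days together make up the preceptorship, so day 2 is the more natural reading.

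| Assumed g | Control T1 / final | Intervention T1 / final (day 2) | Intervention T1 / final (day 1) |
|---|---|---|---|
| 0 | 1 / 13 | 2 / 14 | 1 / 13 |
| 3 | 1 / 13 | 5 / 17 | 4 / 16 |

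T1 to final is 12 months in both arms.

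**3. Room for dilution.** The stated Aim 1 sample size was reproduced first. Inputs from the sample-size section: 21% against 42%, 80% power, chi-square, 30% loss. The 5% level comes from the same section; two-sided is assumed.

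- n per arm = [1.96·√(2·0.315·0.685) + 0.842·√(0.21·0.79 + 0.42·0.58)]² / 0.21² = 76 after rounding up.
- Total 2 × 76 = 152; 152 / 0.70 = 218 after rounding up, against 220 stated. It reproduces.
- With 220 recruited, 220 × 0.70 / 2 = 77 evaluable per arm, and power is 0.807. There is almost no slack.

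As an illustration only, suppose the 21-point effect shrank in proportion to exposure, so that the intervention rate is 0.21 + 0.21 × e/18 for e months. At e = 17, 16, 15 and 12 the rates are 0.408, 0.397, 0.385 and 0.350, and power is 0.76, 0.72, 0.66 and 0.49. The article does not establish that proportionality, so these figures show sensitivity and are not an estimate of power lost.

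**The case against.** The case on the other side has real force.

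- **Measuring patients before training is good design.** It keeps enrolment and baseline free of the intervention. This stands, and the fix keeps it.
- **A reader might infer that the arms' patients are followed for different lengths of time.** They are not: both have 18 months from baseline. The unequal intervals concern professionals only, who come under a secondary aim.
- **A reader might infer that no programme existed when the clock started.** It was developed and delivered in Phase 1; it has only not yet reached that FMG.
- **A reader might infer that chart entries made before training are counted as post-intervention.** The text does not say so. Its 18-month window attaches grammatically to history and medications, and the next sentence, on evaluations and interventions, speaks only of an observation period. The classification is open.
- **The month between training days is not plainly unexposed.** The days are spaced so that participants can apply what they learned, so counting exposure from day 1 is reasonable. Percentages of unexposed time would also need an accrual duration that the article does not give.
- **Loss of the weight effect is not shown.** The Background reports at least 5% weight loss at 12 months in 45-55% of patients in the group's own clinic, and in 33% of all those followed up in a UK primary-care programme. Even g = 6 leaves 11 months after day 2.
- **The professionals' T1 has a rationale**, namely comparability with Phase 1, and simultaneous evaluation is promised only as far as possible. That explains the intervention arm's timing. It does not explain why the control T1 is fixed at 1 month after baseline.

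**Conclusion.** Both timing points hold, at modest size.

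For patients, the exposure named in the primary aims is not what the schedule delivers. It is 18 − g months from the first training day, with g unstated. The consequence is a misdescribed endpoint and some dilution towards no difference. The comparison between arms remains fair, and the sample size of 220 is correctly calculated on its own assumptions. How much effect is lost cannot be derived from the article.

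For professionals, the evaluations fall at different distances from baseline in the two arms: about 2 and 14 months against 1 and 13 if training starts at baseline and T1 is counted from the second day. The difference grows month for month with any delay in training. It disappears only if training starts at baseline and T1 is counted from the first day. This sits badly with the stated wish to evaluate pairs together, although that wish is hedged and so not strictly contradicted.

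The changes should be made because they are cheap and remove a timing difference between arms and a wrong statement of exposure.

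**What to change.** 1. **Professionals.** Set the control FMG's T1 and T1 + 12 months to the same dates, or the same intervals from baseline, as its paired intervention FMG. State which training day the intervention T1 is counted from. No assessments are added; control T1 moves later, and the partner's training date must be known when it is scheduled.
2. **Primary aims.** Restate the endpoint as 18 months from patient baseline. This is a change of wording only.
3. **Gap.** Keep the interval from patient baseline to preceptorship short, record it for each patient and report it by FMG. The cost is one date per FMG.
4. **Chart-review process outcomes.** In both arms, count entries from the paired FMG's preceptorship date as the post-period. State what applies to a control patient whose baseline falls after that date, which can happen because pairing in time is only approximate. Charts are reviewed at the end of the study at each site, so this is a coding rule and needs no new data collection.
5. **Leave the 18-month patient visit anchored on patient baseline.** Moving it to 18 months after training would make the weight-change interval longer and variable between patients, in a trial that already allows for 30% drop-out or incomplete data.

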#### Metabolic markers

We chose metabolic markers not influenced by a fasting state in order to increase feasibility of blood sampling during patient evaluations. We will use HbA1c which correlates with glycemic control in patients with DM2 and is also a marker of dysglycemia which can be used to diagnose pre-diabetic states and DM [47]. Furthermore, HbA1c was identified as a good marker of cardio-vascular events even in non-diabetic individuals [48]. Lipoproteins ApoB (marker of atherogenic LDL particules) and ApoA1 (marker of protective HDL particules) will be used [42,49,50]. Apo B is thought to be a better marker of cardiovascular risk than LDL and a better predictor of treatment benefits [40,49,51]. Furthermore, ApoA1 and ApoB/ApoA1 ratio are expected to improve with weight loss and lifestyle modification and can be used as biomarkers of improved cardio-vascular risk [49,50,52,53]. These will be measured in the CHUS clinical biochemistry laboratory using standard methods.

#### Lifestyle

Physical activity level and eating habits will be measured using a questionnaire adapted from the one used by Statistics Canada for the latest Canadian Health Survey [54]. It inquires about the frequency and duration of active travelling, leisure time, and sedentary activities. We chose this questionnaire since it is easy and quick to complete and allows comparison of the characteristics of our patients to those of the general Canadian population.

#### Fitness level

Since objective measurements of exercise capacity in patients are usually better than self-reports, we will use the six-minute walk test (6MWT), a simple index that estimates functional capacity in obese subjects and is also a predictor of morbidity and mortality [55–57]. The 6MWT is a simple test that we will be performed in FMGs where the environment permits according to the protocol recommended by the American Thoracic Society, and measures the distance that a patient can quickly walk in a period of 6 minutes [58]. It has been shown that weight loss increases functional capacity, as measured by the 6MWT, early in the weight loss process, making this test a very accurate tool to evaluate the impact of the intervention on obese/overweight patients’ functional capacity [59–61].

#### Readiness for change

In the course of previous prospective studies, we have designed a 22-question weight loss readiness tool (WLRT) based on Prochaska and DiClemente’s Stages of Change Model, which is currently being validated [4,62]. It evaluates the motivational readiness of patients regarding weight management, nutrition and physical activity, and could predict response to an intervention. Our WLRT takes 5-10 minutes to fill out, making it a clinically applicable tool. It has been useful to identify subjects with greater chances of success for lifestyle modification in previous studies of our group [63,64]. Its predictive value will be assessed in this study, but it will also serve to explore the mechanisms of potential benefits of our intervention and for stratified analyses.

#### Conformity to CCM

We will be using the Patient Assessment of Chronic Illness Care questionnaire (PACIC), developed and validated by the McColl Institute to evaluate perceived concordance of received care with the CCM [18,20,21]. We used the World Health Organization process of translation and adaptation of instruments to translate the questionnaire into French [65].

#### Perceptions and satisfaction of patients

Patient perceptions of their personal experience regarding weight management and their satisfaction regarding management by their health professionals will be evaluated with questionnaires that we designed based on previous studies. A qualitative in-depth analysis of patients’ perceptions will also enhance our understanding of their personal experience with the care received for lifestyle optimization in FMGs. Eight to ten patient volunteers will be recruited in each FMG to participate in a taped-recorded semi-structured qualitative interview to assess their perceptions of impact of the program (continuity of care, perceptions of changes, contribution to change, quality of life, perspectives of future changes, explanation of level of satisfaction with the program). An interview guide with open-ended questions derived/adapted from the principal variables of the study, the Diabetic Empowerment Scale (DES) [16], and the Weight-related Quality of Life (WQOL-lite) questionnaire [66] will be used as in previous studies from members of our group [33,67].

#### Evaluation of health professionals (PCPs and nurses)

All evaluations will take place at baseline, T1 (1 month after the preceptorship for the intervention group and 1 month after baseline for the control group) and 12 months after T1 in order to compare the data collected during our Phase 1 study and to compare intervention and control groups. The same questionnaires that we developed and validated will be used to evaluate Aim 3 of this proposal. We have slightly modified some tools based on the results of our Phase 1 project. Results will be correlated to patients’ outcome.

#### Attitudes, perceptions and self-efficacy toward obesity management

Self-efficacy is defined as the set of beliefs about one’s capabilities to perform at a designated level [68]. For health professionals to engage in weight management with their patients, they must not only accept this as part of their role but also feel that they are competent to accomplish the task. Indeed, 3 stages were identified in physician learning [69]: i) deciding whether to take on a learning task to address a problem; ii) learning the skill and knowledge anticipated to resolve the problem and iii) gaining experience in using what has been learned. Negative attitudes toward obese individuals and perceptions to the effect that available treatments are ineffective (as found at baseline in our Phase-1 study), can prevent the engagement of health professionals in weight management [24,25,70]. Thus, by providing participants with the necessary knowledge, skills and continued support to undertake weight management with their patients, we believe that we will be able to initiate what Tiberius and Tipping considered a “healthy spiral”: beginning with an acceptance of inherent challenges (related to weight management) and moving to success at those tasks (helping patients) and finally to the development (through experience) of a more positive sense of self-efficacy [71]. Changes in attitudes and perceptions could be correlated to changes in practice and patient outcomes. This will be evaluated using questionnaires that we developed in our previous project based on the literature.

#### Knowledge and expertise on obesity management

To assess the impact of our intervention on medical knowledge regarding obesity, physicians and nurses will be asked to respond to a short-answer and multiple-choice questionnaire of 25 questions. The questionnaire will address topics related to obesity management such as physical activity and nutritional recommendations a and non-obesity related topics such as management of hypertension or tobacco cessation.

